## 1.3 Schedule of Activities (SoA)

| **Procedure** | **Day 0-1***  **Enrollment** | **Day 7 +/- 1** | **Day 30 +/- 5 End of Study** |
| --- | --- | --- | --- |
| Screening and eligibility | X |  |  |
| Medical history | X |  |  |
| Consent | X |  |  |
| Demographics/baseline information | X |  |  |
| Concomitant medication review | X | X |  |
| ED/Hospital admission data collection** | X | X |  |
| Randomize to “use next box” | X |  |  |
| Administer study nebulization 1 | X |  |  |
| Administer study nebulization 2 | X |  |  |
| Administer study nebulization 3 | X |  |  |
| Surgical hemorrhage control (Y/N) | X | X |  |
| 1st TXA Level (last neb up to 60 mins) | X |  |  |
| 2nd TXA Level (60 mins to 8 hours) *** | X |  |  |
| ENT OR decision survey | X |  |  |
| Process, freeze, store, and ship samples | X |  |  |
| Age-appropriate Pain Scale |  | X |  |
| Parents and Children (Promis Anxiety Scale 8a) |  | X |  |
| Adverse and serious adverse events | X | X | X |

*Randomization to 24 hours

**Should include the following, if collected per standard of care: vital signs (including height and weight), physical exam, ENT upper airway exam, lab data collection (coagulation labs, other routine lab tests), OR use, ENT exam & findings as relating to OR use (e.g., photo of tonsillar bed), blood product usage, final hospital disposition. At seven days, further, evaluate if participants had been readmitted for bleeding after an intervention.

***Time points must be separated by 60 to 90 minutes.

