Nebulization of TXA is not a common route of administration compared to oral or intravenous delivery. Inhaled or intranasal medication can be rapidly absorbed across the large surface area of the respiratory tract epithelium. Some drugs absorbed into the pulmonary circulation enter directly into the systemic circulation via the pulmonary vein, possibly bypassing first-pass metabolism that occurs with oral drugs. Previous research into the site of action for inhaled medications has been limited to animal studies because biopsy of the entry site would be dangerous to the subject. However, to choose the optimal dose it is important for investigators to understand the level of absorption at the topical and systematic level. Typical pharmacokinetics of TXA cannot be done in this study, however the concentrations can be estimated by verifying physiologically based pharmacokinetic (PBPK) model designed to predict the change in pharmacokinetics that occur as the inhaled drug cross the respiratory epithelium. A pulmonary PBPK model begins with extracting from the literature all known pharmacokinetic data on the inhaled drug and the known properties for absorption and metabolism across the respiratory epithelium. Fortunately, several pharmacokinetic studies using healthy adults or animals have been performed with TXA. Additionally, several pediatric and inhaled pharmacokinetic studies are available. Utilizing this data, we can build a PBPK model to predict the level of topical and systematic absorption. The main advantage of this method is to understand how an inhaled drug is absorbed and metabolized in the respiratory epithelium with the fewest number of systematic samples. Instead of collecting a wide range of samples from different ages and doses, we only need a few samples to verify that the parameters used to build the model were correct. This technique has been used in multiple studies to predict the dosing response in various populations or using different routes of administration.

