# 3 Objectives and Endpoints

| OBJECTIVES | ENDPOINTS | JUSTIFICATION FOR ENDPOINTS |
| --- | --- | --- |
| Primary | | |
| Evaluate the feasibility to enroll 0.6 patients/site/month  Nebulize at least two of three doses of TXA to children with PTH.  Determine the local and systematic concentrations of nebulized TXA in children  Determine incidence of adverse and serious adverse events | Enrollment after one year and % of nebulization’s. Go/no-go threshold is 0.6 patients per site per month for a total of 22 patients. Time and success to obtain consent will establish need for exception for informed consent (EFIC).    The goal is >90% of patients will receive at least two of three planned nebulization of TXA.  Collection of two blood samples from each participant. This will verify a pulmonary physiological-based PK model (PBPK) (i.e., nasal cavity, pharynx, and lung) that indirectly predicts the oropharyngeal and systematic concentration of nebulized TXA.  A phone call or email will be placed to participants at 30 +/- 5 days. | The overall incidence of PTH is 5%, yet numbers per site may be very different. Assessment and consent will optimize site selection, recruitment process, and the plan the main trial.    The establishment of a pragmatic protocol design will help design a large trial.  Limited data on nebulized TXA systematic absorption. Topical PK studies of TXA document a significant reduction in systematic levels but the same hemostasis effect.  Safety Evaluation as recommended by the FDA. |
| Secondary | | |
| Determine the number and rationale for PTH patients to return to the OR; and    Determine the number of blood transfusions and estimated blood loss and      Determine the recurrence of PTH after TXA, saline, or return to the OR. | Collection number participants and surveys on ENT surgeons’ decision to go to the OR    Collection of electronic health record data on number of blood transfusions and estimated blood loss    Survey families to determine PTH recurred seven days from randomization. | To evaluate if return to the OR can be an outcome for the main trial.    To evaluate if TXA decreased severity of PTH bleeding.      To evaluate if TXA or return to OR prevented PTH recurrence. |
| Tertiary/Exploratory | | |

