**Pharmacokinetic and Pharmacodynamic Testing:** Pharmacokinetics samples will be collected after completion of the last nebulized treatment received within sixty minutes. A second time point should then be collected after sixty minutes up to eight hours from last nebulization, separated from the previous time point by at least sixty to ninety minutes. The results from the TXA level measurements will be used for research purposes only and not be available to clinicians. The serum TXA levels will be used to develop a TXA PK model and determine the population variability. We will develop a base model to determine a best-fit compartmental model, distribution, and elimination kinetics. We will also use stochastic models to evaluate between-subject variability in PK parameters. Serum TXA concentrations will use 200 microliters of plasma measured by an ultra-high performance liquid chromatography tandem mass spectrometry method specifically developed for sensitive and precise analysis of low TXA concentrations at the U.S. Army Institute for Surgical Research. Moreover, we will use the remaining 200 microliters to measure pharmacodynamics effects of nebulized TXA in the plasma. ELISA can use minimal plasma volume (<300 μL) to run commercial kits measuring Plasmin-antiplasmin (PAP) complexes, D-dimer, Thrombin-antithrombin (TAT) complexes, Prothrombin fragment F1+2 (F1+2), and Plasminogen activator inhibitor-1 (PAI-1). Combination of pharmacokinetic and pharmacodynamic effects achieves the primary goal to determine drug systematic compared to local effects.

The protocol will adhere to the following guidelines when scheduling procedures to collect pharmacokinetic samples:

- Samples will be collected in EDTA 1 mL tubes (Fisher Scientific Catalog number 22-030-402). Within 2 hours of sample collection, tube will spin in a calibrated centrifuge. Please see attached centrifuge calibration standard of operating procedure.
- Centrifuge procedures consist of:
  - Place sample in centrifuge with appropriate weighted balance
  - Centrifuge sample at 2500 RPM for ten minutes at room temperature
  - Remove sample from centrifuge, using a pipette remove plasma above buffy coat and place into a clean Eppendorf tube (roughly 0.4-0.6 mL).
  - Place Eppendorf tube back in centrifuge with appropriate balance.
  - Centrifuge second time at 2500 RPM for ten minutes at room temperature.

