# 9 Statistical Considerations

## 9.1 Statistical Hypotheses

The pilot study is not designed to test an efficacy hypothesis, but rather to determine the feasibility for patient enrollment and the number of doses received per patient.

**Our primary hypothesis** for the single site and the multi-site study is that we can enroll at least 0.6 patients per site per month and deliver a minimum of two out of three planned nebulized TXA doses to >90% of enrolled patients.  The single site study will only be one year and the multi-site study for 18 months. We will test each of this (yes/no) hypothesis using a Mantel Haenszel test stratified by site for a total of 12 patients for the single-site study for greater than 24 nebulization and for the multi-site study up to 22 patients with greater than 44 nebulization's recorded as delivered.

**Our secondary goals** will be to determine if nebulized TXA prevents going to the OR for PTH and utilization of blood products. These goals are not powered to be tested in the pilot study. **Our second aim** is to verify a pulmonary physiological based pharmacokinetic (PBPK) model (i.e., nasal cavity, pharynx, and lungs) will predict the change in the area under the curve (AUC0-α) of TXA concentration in systemic compartments with accuracy (average absolute fold error <2) and precision (average fold error <2). We will calculate the AUC of accuracy and precision of the model using the linear trapezoid rule. For the PBPK model, we will use previously published PK data to construct the model before verifying it with systematic samples.

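### Section 9.1 judges the PBPK model on a trapezoid AUC that two post-dose samples cannot supply and that conflicts with Section 9.4.3, and the schedule's sampling-gap footnote conflicts with its own 8-hour window

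*Protocol*

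**What the plan says.** Section 9.1 sets as the second aim that the PBPK model will "predict the change in the area under the curve (AUC0-α) of TXA concentration in systemic compartments with accuracy (average absolute fold error <2"), with an average fold error below 2 as the precision limit. It adds "We will calculate the AUC of accuracy and precision of the model using the linear trapezoid rule". On the source of the data it says "we will use previously published PK data to construct the model before verifying it with systematic samples".

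The data are described in three places. Section 3 lists "Collection of two blood samples from each participant". The schedule in Section 1.3 times the first as "1st TXA Level (last neb up to 60 mins") and the second from 60 minutes to 8 hours, and its footnote says "Time points must be separated by 60 to 90 minutes". Section 8.2.2 places the first sample within an hour of the last nebulization received. It continues "A second time point should then be collected after sixty minutes up to eight hours from last nebulization", and it gives the 60 to 90 minute interval as a minimum, with no ceiling.

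Section 9.4.3 gives another way of accepting the model. Simulated concentrations are compared with observed ones, using AFE limits of 0.7 to 1.3, an AAFE of at most 2, and 90% of observations inside the 5th to 95th percentile prediction interval. It does not mention AUC.

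**The concern.** A fold error in AUC needs an observed AUC as well as a predicted one. The plan takes no sample before, during or between the nebulizations and states no rule for extrapolating beyond the second sample. The test in 9.1 therefore has no observed side. Section 2.2 comes close to saying so: "Typical pharmacokinetics of TXA cannot be done in this study".

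Section 4.2 says the verified model can set the phase 3 dose, so it matters that the acceptance rule is single and can be carried out. With two different rules in the protocol, the choice between them could be made after the data are seen.

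The timing conflict matters for conduct. A site that draws the second sample at 6 hours complies with 8.2.2 but deviates from the schedule's footnote.

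**Working it through.** **1. Timing (no assumptions needed).** Inputs from Section 1.3: first sample t1 = 0 to 60 min after the last nebulization; second-sample window 60 to 480 min; footnote gap g = 60 to 90 min.

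- Second sample: t2 = t1 + g. Latest value: 60 + 90 = 150 min (2.5 h), against the stated 480 min.
- Share of the stated window that can be reached: (150 − 60)/(480 − 60) = 90/420 = 21%.
- A sample at 480 min would need t1 between 480 − 90 = 390 and 480 − 60 = 420 min, outside the first sample's own window.
- Under 8.2.2, where the interval is a minimum, t2 = 480 min is allowed for any t1 from 0 to 60 min (gaps of 420 to 480 min), and the conflict disappears.

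**2. What the trapezoid covers.** With two concentrations C1 and C2, the rule gives one area, (C1 + C2)/2 × (t2 − t1). The full AUC also contains the area before t1, including all accumulation during the nebulizations, and the area after t2. Neither is sampled in any child, so pooling children does not recover the part before the last dose ends.

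**3. How large the gap could be (illustration).** The protocol gives no PK parameters. Section 8.2.1 equates 24 hours with more than 5 half-lives, so the half-life is below 24/5 = 4.8 h. Assumptions: one compartment, a single first-order input starting at the last nebulization, elimination half-life 1, 2, 3 or 4.8 h, absorption half-life 0.1 or 0.5 h. For unit dose and volume:

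C(t) = ka/(ka − k) × (e^(−kt) − e^(−ka·t)), with true AUC = 1/k.

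Worked case: elimination half-life 2 h (k = 0.3466), absorption half-life 0.1 h (ka = 6.931), samples at 0.5 and 1.75 h. C1 = 0.852 and C2 = 0.574, so the trapezoid is 0.713 × 1.25 = 0.891. True AUC = 2.885, and the ratio is 0.31.

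| Sample times | Two-point trapezoid / true AUC, over all assumed half-lives |
|---|---|
| Within the footnote: 0.1/1.1 h, 0.5/1.75 h, 1/2.5 h | 6% to 47% |
| Second sample at 8 h: 0.5/8 h, 1/8 h | 45% to 196% |

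Anchoring the curve at an assumed zero concentration at time zero changes these ranges to 6% to 60% and 47% to 209%. Without that anchor, every footnote-compatible case is short by more than 2-fold (1/0.47 = 2.1). So the error from sampling alone can exceed the 2-fold limit in 9.1, whatever the quality of the model.

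**4. The two acceptance rules side by side.**

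| | Section 9.1 | Section 9.4.3 |
|---|---|---|
| Quantity | AUC0-α | Concentrations at sampled times |
| AFE | < 2, called precision | 0.7 to 1.3, called bias |
| AAFE | < 2, called accuracy | ≤ 2, called precision |
| Coverage | none | 90% inside the 5th–95th percentile interval |

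Suppose a model over-predicts every concentration by 50%. Then AFE = AAFE = 1.5, and the AUC is over-predicted by the same factor. It meets the 9.1 limits and fails the AFE limit in 9.4.3.

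**The case against.** The strongest reply is that verification does not depend on the AUC sentence. Section 9.4.3 gives a complete concentration-based rule that two samples per child can feed, and Sections 2.2, 4.2 and 9.1 say that published data build the model while the trial's samples only check it. This stands. A reader might infer that the model cannot be verified at all, and the protocol does not support that.

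A reader might also infer that a primary objective fails. The documents do not settle its status. Sections 1.1 and 3 list TXA concentrations as primary, but the attached endpoint is the collection of two samples. Section 8.1 calls the work secondary, 9.1 a second aim, and 9.4.3 a secondary outcome.

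The trapezoid rule is legitimate on a densely simulated curve, and 9.1 does not say which curve it means. It could also be applied to predicted and observed values at the same two times. That yields a partial area built from the two concentrations. It is not AUC0-α and adds no data to what 9.4.3 already uses. The upper limit is printed as α, and infinity is a reading. If it means the last sample, the input phase is still missing.

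On timing, the footnote may simply have lost the words that make the gap a minimum. That is plausible, since the schedule's own row and 8.2.2 both allow 8 hours. The claim that all samples fall within 2.5 hours would hold only if the footnote overrides both.

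Two further inferences fail. The compartmental model with between-subject variability in 8.2.2 does not contradict 2.2, because pooled sparse-sample population modelling is accepted practice and 2.2 may refer only to rich sampling. Poor precision of a single child's elimination slope enters no acceptance test in 9.1 or 9.4.3.

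**Conclusion.** The point holds in two parts.

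First, the AUC criterion in 9.1 cannot be evaluated from the trial's samples, and it competes with a feasible rule in 9.4.3 that has different limits and labels. This follows from the sampling plan alone. The percentages depend on the assumed one-compartment model and half-lives and only show the possible scale.

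Second, the schedule's footnote limits the second sample to 150 minutes where the same table and 8.2.2 allow 480. That result rests on the literal text and on no PK assumption. The documents do not settle which wording governs.

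Neither part prevents verification of the model against concentrations. Both should be corrected, because the verified model is meant to inform the phase 3 dose.

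**What to change.** - **Section 9.1:** replace the AUC and trapezoid criterion with the concentration-based criterion of 9.4.3 as the single acceptance rule. State one set of AFE and AAFE limits, with one set of labels, in both sections.
- **AUC:** report it as a quantity derived from the model and say that it is not directly verified by the trial's samples.
- **Section 1.3 footnote:** reconcile it with the schedule's second-sample window and with 8.2.2. Wording the gap as a minimum would make the 8-hour window usable; keeping an upper bound would mean shortening the window in both places.

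The cost is wording in Sections 9.1, 9.4.3 and 1.3, plus 8.2.2 if the window is shortened, with no extra blood draws. The drawback is that any statement about AUC becomes model-based only.

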## 9.2 Sample Size Determination

Multiple studies suggest that 76% of children with PTH go to the OR for surgical control of their hemorrhage. This pilot study sample size is based on the goals for the subsequent phase 3 trial. Conservatively, we estimate that nebulized TXA will decrease the incidence of surgical care for PTH from 76% to 61%, or in other words a 15% effect size.  The sample size for phase 3 trial based on an effect size of 0.15 with randomization of 324 children with PTH using an a priori, one-tailed, Fishers exact test stratified by site, with 80% power, alpha=0.025. This trial will then need to enroll at least 0.6 patients per site per month at 12 sites over 4 years (0.563 patients x 12 sites x 48 months = 345 patients). Thus, the go/no-go threshold for the subsequent phase 3 trial is an enrollment goal of 0.6 patients per site per month in this pilot study. For the single site trial designed for one year, we hope to enroll 12 patients. For the mutli-site study we hope to enroll 22 patients’ across 3 enrolling sites over 12 months at 0.6 patients x 3 sites x 12 months = 21.6, rounded up to 22 targeted enrollments.

## 9.3 Populations for Analyses

A. Received nebulized TXA

B. Received nebulized saline (placebo control)

## 9.4 Statistical Analyses

### 9.4.1 General Approach

The pilot trial is not powered to evaluate efficacy. Feasibility, efficacy, and safety outcomes will undergo descriptive analysis.

### 9.4.2 Analysis of the Primary Efficacy Endpoint(s)

Differences between TXA and saline conditions with respect to the primary outcome (i.e., need for surgical intervention: yes or no) will be analyzed statistically using the Mantel Haenszel test stratified by site.

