### 2.3.2 Known Potential Benefits

The study's primary outcome is the need to go back to the operating room for hemostatic control within 24 hours from randomization. Although repeat surgery can restore hemostasis for post-tonsillectomy hemorrhage, it is not a guarantee of success. One small study of nonactive bleeding patients documented that the rate of rebleeding was 26/203 (12.8%) after inpatient observation and 3/21 (14.3%) after an operative intervention^5^. Our review of studies has revealed a modestly increased risk of adverse neurodevelopmental outcomes in children exposed to a single episode of general anesthesia and compounds with multiple exposures^15^.  Therefore, a reduction in exposure to a second surgery involving cauterization, anesthesia, and anxiety would significantly benefit children with post-tonsillectomy hemorrhage. Moreover, research into non-operative interventions will help future children who suffer from aerodigestive bleeding.  The benefits can be further classified into two groups:

A. **Immediate Potential Benefits**

1. Prevention of the need to return to the operating room for cauterization

2. Decrease in acute pain and anxiety in avoiding a procedure.

B. **Long-term benefits**

1. Reduction in anesthesia exposure may improve neurodevelopmental outcomes.
2. Avoidance of secondary procedure may improve early return to normal activities and improved quality of life in terms of benefits of the initial tonsillectomy including reduction of tonsillitis and sleep apnea symptoms.
3. The pilot study will inform an improved study design for a larger trial.
4. The pilot study will verify a PBPK model that will provide useful information on dosing and absorption of the nebulized TXA.

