# 4 Study Design

## 4.1 Overall Design

Our overall hypothesis for the phase 3 trial is that nebulized TXA will decrease the severity of bleeding and the need for repeat surgical intervention for PTH. To test this hypothesis, we first propose to conduct a multi-center, randomized controlled, blinded pilot trial (phase 2) to assess the feasibility, safety, and the local and systematic absorption of nebulized TXA in children with PTH. Safety and pharmacokinetic data are well known for topical and intravenous administration of TXA but there is limited data on nebulized delivery of TXA. Participants will be randomized at the time of the consent in the emergency department. Earlier PECARN studies experience suggest that pre-consenting patients in surgical clinic will not improve participant enrollment or completion. Children 2 to 17 years old presenting to the ED with PTH will be randomized in a 1:1 ratio to three doses TXA or placebo (saline).  All interventions will be blinded by the investigator, treating clinical care team, and research staff. Only the pharmacist and biostatistician will know the randomization schedule. We will not unblind patients as there is no reversal agent. Clinical teams will be asked to assume the patient received TXA. Patients will be followed during their hospital course and outcomes will be evaluated at seven +/- 1 days after randomization. As this is a pilot study, no stratification or interim analysis will be performed.

[figure not shown]

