# 8 Study Assessments and Procedures

## 8.1 Efficacy Assessments

The **primary feasibility outcomes** for the pilot trial are the enrollment rate (patients per site per month) and the proportion of patients receiving study drugs (at least 2 nebulized doses).  Safety is always an outcome, and all adverse events will be reviewed.

**The secondary outcome is** the ENT surgeon rationale, decision (Y/N) for the PTH patient to return to the OR, severity of bleeding with estimates of blood loss that include volume of hemorrhage recorded blood loss, and the number of blood transfusions. Additionally, we will determine the indirect local and systematic concentration of nebulized TXA by verifying our pulmonary physiologically based pharmacokinetic model. To verify the model, two lab samples will collect at opportunistic times either by finger stick or ad**. The study is not** powered for the secondary outcomes as this a pilot trial.

The **exploratory outcomes** will be age-appropriate pain scores and parent and child anxiety scales as measured by anxiety-state-trait scale (STAI). For children under eight years old their anxiety will be measured by STAI-C, which utilized pictures These will be exploratory as the pilot trial is not powered to determine the change in the outcomes.  Please see **Figure 7** for a timeline of all study procedures and outcomes.

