## 8.2.4 FOLLOW UP DATA COLLECTION

**The secondary outcome** (the need for return to the OR for surgical management of PTH) will be followed for up to seven days after randomization.

**Patient-related outcomes measures (PROM)** include pain (as measured by age-appropriate pain scale) and parental/patient anxiety (measured at 7 days after randomization).  The rationale for measuring parent and child anxiety and pain have been documented as measures that significantly predict overall parent satisfaction with perioperative care^28^. To assess patient and parent-centered outcomes of parental and child anxiety we will assess the following scores at day 7 +/- 1-day post-study drug randomization.

1. PROMIS Short Form v1.0 - Anxiety - 8a 31 May2019, PROMIS Early Childhood Parent Report SF v1.0 - Anxiety 8a - 4-1-2021, and Numeric Rating Scale for Anxiety (NRS-A)
2. Wong-Baker Age-appropriate Pain Score & FLACC Behavioral Assessment Scale

For discharged patients, parents will be contacted by a HIPAA compliant text messaging (e.g., TigerConnect App) or phone call for these assessments and communication. If the patient is still in the hospital, research staff may conduct these follow-ups in person.

Wong-Baker FACES® Pain Score:

[figure not shown]

 FLACC Behavioral Pain Assessment Scale

**Parental and child state and trait anxiety**: To assess anxiety in both parents and pediatric participants, we will use validated Patient-Reported Outcomes Measurement Information System (PROMIS) instruments and a Numeric Rating Scale for Anxiety (NRS-A).

1. PROMIS Anxiety Measures

Older children, adolescents, and parents: Anxiety will be measured using the PROMIS Short Form v1.0 – Anxiety – 8a (31 May 2019). This is an 8-item self-report instrument designed to assess symptoms of fear, worry, hyperarousal, and somatic anxiety over the past 7 days. Items are scored on a 5-point Likert scale (Never to Always). Raw scores are converted to standardized T-scores (mean 50, SD 10), allowing comparison to the U.S. general population. Higher T-scores indicate greater anxiety severity.

Young children (early childhood): For children aged 4–7 years, anxiety will be assessed using the PROMIS Early Childhood Parent Report Short Form v1.0 – Anxiety 8a (April 1, 2021). This parent-reported instrument captures observable anxiety-related behaviors and symptoms in young children. It includes 8 items scored on a 5-point response scale and similarly generates standardized T-scores.

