### 10.1.2 Study Discontinuation and Closure

This study may be temporarily suspended or prematurely terminated if there is sufficient reasonable cause.  Written notification, documenting the reason for study suspension or termination, will be provided by the suspending, or terminating party to study participants, investigator, funding agency, the Investigational New Drug (IND) sponsor and regulatory authorities.  If the study is prematurely terminated or suspended, the Sponsor/Principal Investigator (PI) will promptly inform study participants, the IRB, and the FDA and will provide the reason(s) for the termination or suspension.  Study participants will be contacted, as applicable, and be informed of changes to the study visit schedule.

Circumstances that may warrant termination or suspension include, but are not limited to:

- Determination of unexpected, significant, or unacceptable risk to participants
- Demonstration of efficacy that would warrant stopping.
- Insufficient compliance to protocol requirements
- Data that are not sufficiently complete and/or valuable
- A determination that the primary endpoint has been met
- Determination of futility

The study may resume once concerns about safety, protocol compliance, and data quality are addressed, and satisfy the sponsor, IRB, and/or Food and Drug Administration (FDA).

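### Sections 9.4.2 and 2.3.2 make return to the operating room the primary outcome, and 9.4.2 tests it between arms, although the rest of the protocol makes it a secondary, descriptive outcome; its time window also varies

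*Protocol*

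**What the plan says.** **Return to the operating room (OR) as primary.** Section 9.4.2, headed as the analysis of the primary efficacy endpoint, says that TXA–saline differences on the "primary outcome (i.e., need for surgical intervention: yes or no) will be analyzed statistically using the Mantel Haenszel test stratified by site". Section 2.3.2 says that the study's "primary outcome is the need to go back to the operating room for hemostatic control within 24 hours from randomization".

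**Return to the OR as secondary.** Section 8.1 says that the outcomes it ranks as primary in this "pilot trial are the enrollment rate (patients per site per month) and the proportion of patients receiving study drugs (at least 2 nebulized doses"), and lists the OR decision among the secondary outcomes. Section 3 puts "Determine the number and rationale for PTH patients to return to the OR" under secondary objectives, as does the synopsis. Section 8.2.4 labels "the need for return to the OR for surgical management of PTH" the secondary outcome. Section 9.1 states: "The pilot study is not designed to test an efficacy hypothesis". It then lists prevention of OR visits among secondary goals that are not powered for testing.

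**Type of analysis.** Section 9.4.1, directly before 9.4.2, says that feasibility, efficacy and safety outcomes will be analysed descriptively.

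**Window.** Section 2.3.2 gives 24 hours from randomization. Section 8.2.4 gives up to seven days. Sections 4.4 and 7.3 refer to seven to thirty days. Section 9.4.2 gives none.

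**The concern.** The protocol fixes two incompatible answers to two basic questions: which outcome is primary, and whether efficacy is tested or described. A later analysis plan cannot fill this as a gap. If it follows 9.4.2 it departs from 9.1 and 9.4.1, and if it follows those it departs from 9.4.2.

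Followed literally, 9.4.2 would make a between-arm p-value the formal primary result of a study built to measure enrolment and dose delivery. A non-significant p-value could be misread as a failed primary analysis, and a chance significant one as evidence of efficacy. Because the outcome in 9.4.2 has no window and the schedule records surgical control at two visits, the events to be counted could be chosen after the data are seen.

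**Working it through.** **1. Label and analysis, side by side**

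| Protocol section | Status of return to OR | Analysis |
|---|---|---|
| Synopsis (1.1), Section 3 | Secondary | not stated |
| 8.1 | Secondary; not powered | not stated |
| 8.2.4 | Secondary | not stated |
| 9.1 | Secondary goal | not powered for testing; no efficacy hypothesis |
| 9.4.1 | not stated | Descriptive |
| 2.3.2 | **Primary** | not stated |
| 9.4.2 | **Primary** | **Mantel-Haenszel test, TXA versus saline, by site** |

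Two sections stand against the rest on the label, and 9.4.2 stands against 9.1 and 9.4.1 on the analysis.

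**2. Window**

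| Section | Window |
|---|---|
| 2.3.2 | 24 hours from randomization |
| 8.2.4 | up to 7 days from randomization |
| 7.3 | 7 to 30 days from randomization |
| 4.4 | 7 to 30 days from receipt of study drug |
| 9.4.2 | none |

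The Schedule of Activities (1.3) records surgical control at Day 0-1 (randomization to 24 hours) and Day 7 ± 1, but not at Day 30. The data can therefore serve the first two windows. The third has no scheduled assessment of this outcome after Day 7.

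**3. What the 9.4.2 test could show (context only)**

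Inputs: surgery rates of 76% and 61% (9.2); 1:1 allocation (4.1); 6 versus 6 (5.5); 22 patients, so 11 versus 11 (9.2); up to 30 patients, so 15 versus 15 (synopsis). No significance level is stated for the pilot, so two-sided 5% is an assumption.

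*The plan's own figure first.* Section 9.2 gives 324 children for phase 3 (one-sided 0.025, 80% power, Fisher's exact test). With mean rate 0.685:

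n₀ = [1.960·√(2·0.685·0.315) + 0.842·√(0.76·0.24 + 0.61·0.39)]² / 0.15² = 149.4 per arm.

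With continuity correction, n = (n₀/4)·[1 + √(1 + 4/(n₀·0.15))]² = 162.4, so 163 per arm or 326 in total. Exact Fisher power at 162 per arm (324 in total) is 80.1%. The figure reproduces, so the inputs are being read as intended.

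*Pilot.* Let x and y be the surgeries per arm of n, M = x + y and N = 2n. The single-stratum statistic is z = (x − M/2) / √[n²M(N − M) / (N²(N − 1))], with rejection when |z| ≥ 1.96. Power is the sum of the binomial probabilities of all rejecting tables.

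| Arms | Mantel-Haenszel, uncorrected | Continuity-corrected | Fisher |
|---|---|---|---|
| 6 vs 6 | 4.9% | 0.9% | 0.9% |
| 11 vs 11 | 10.5% | 4.5% | 4.5% |
| 15 vs 15 | 11.9% | 6.0% | 6.3% |

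At 6 versus 6 the uncorrected test rejects only when the arms differ by four or more children: 6 versus 2 gives z = 2/√(32/44) = 2.35, while 6 versus 3 gives z = 1.5/√(27/44) = 1.91. Simulating three strata gives 11.3% uncorrected and 4.0% corrected at 22 patients, and 13.2% and 6.5% at 30.

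*Sensitivity to the effect.* If the 44% decrease cited in 2.1 and 4.3 is read as a relative reduction, the TXA rate is 0.76 × 0.56 = 42.6%, and uncorrected power is about 18%, 37% and 44% at 12, 22 and 30 patients.

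**The case against.** **Labelling.** Under a heading about the primary efficacy endpoint, the primary outcome can be read as the lead efficacy outcome, distinct from the primary feasibility outcomes of 8.1. This softens the clash of labels in 9.4.2. It does not rescue 2.3.2, which calls it the study's primary outcome without qualification, and it does not reconcile the test in 9.4.2 with 9.1 and 9.4.1.

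**Consequence.** Progression rests on 0.6 patients per site per month (Sections 3 and 9.2), alongside the goal of two doses in more than 90% of patients (Sections 3 and 9.1). A reader might infer that the go/no-go decision depends on the efficacy test; it does not. What is at stake is the formal primary result and how it is reported.

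**Power.** A reader might take the low power as a design error. It is not: 8.1, 9.1 and 9.4.1 say openly that the pilot is not powered for this.

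**Coverage of Section 9.4.** A reader might infer that 9.4 ignores the real primary endpoints. It does not: 9.4.1 covers feasibility descriptively, 9.4.3 covers the pharmacokinetic model and 9.4.4 covers safety. Only a specific method for the enrolment and dose criteria is absent from 9.4, and 9.1 assigns them a Mantel-Haenszel test.

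**Stratification and stopping.** Stratifying by site with one site is harmless, since it reduces to a single-stratum test and the same wording serves the three-site stage. Section 10.1.2 lists "Demonstration of efficacy that would warrant stopping" and futility as possible grounds for termination, while 4.1 says: "As this is a pilot study, no stratification or interim analysis will be performed". The list is generic and schedules no interim look, so it is not a direct contradiction and its bullets need not be deleted on this ground.

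**Conclusion.** The point holds as a contradiction in the text. Sections 2.3.2 and 9.4.2 name return to the OR as the primary outcome, and 9.4.2 tests it between arms. The synopsis, Sections 3, 8.1, 8.2.4 and 9.1 make it secondary, and 9.4.1 makes efficacy descriptive. The outcome also has three windows, and 9.4.2 adopts none of them. This conclusion rests on the wording alone and needs no numerical assumption.

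The power figures only show how little the prescribed test could say. They depend on the 76% versus 61% assumption and an assumed two-sided 5% level. Over test variants at that effect they run from about 1% to 14%, and a larger assumed effect raises them. They do not support calling a non-significant result certain, nor calling the sample size wrong for a feasibility pilot.

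A related inconsistency belongs in the same correction. The synopsis and Section 3 list four primary objectives (enrolment, dose delivery, TXA concentrations, adverse events), while 8.1 and 9.4.3 treat the pharmacokinetic work as secondary.

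**What to change.** - **9.4.2:** make this the analysis of the primary feasibility criteria: enrolment rate against 0.6 patients per site per month, and the proportion receiving at least two of three doses against more than 90%. Report each as a point estimate with an exact confidence interval.
- **9.1:** replace the Mantel-Haenszel wording for these two criteria to match. That test compares groups, whereas these criteria compare one rate or proportion with a fixed benchmark.
- **9.4.3:** add return to the OR as a descriptive secondary outcome, with counts by arm and a risk difference with confidence interval, and no significance test.
- **Window:** name one window in advance and reconcile 2.3.2, 4.4, 7.3 and 8.2.4 to it.
- **2.3.2:** call return to the OR the planned phase 3 primary outcome.
- **Pharmacokinetics and safety:** state consistently whether pharmacokinetics is primary (synopsis, Section 3) or secondary (8.1, 9.4.3), and keep adverse events under 9.4.4.

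The cost is protocol wording only. The schedule already records surgical control at Day 0-1 and Day 7, so choosing either of those windows needs no new data. What is given up is a p-value that the protocol itself says the pilot is not powered to support.
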